# TRIAL TREATMENTS

## Arm 1 -OK432

OK432 is a heat-treated, penicillin-killed lyophilised streptococcal preparation derived from the SU strain of Streptococcus pyogenes group A2 (Picibanil, Chugai Pharmaceutical Ltd, Tokyo, Japan). It is composed of dried streptococcal cells containing penicillin G potassium at a dose of 26,900 units/mg of dried cocci. A dose of 1 (KE) is equivalent to 0.1 mg of dried streptococci. OK432 is supplied as a dry white powder in vials of 1KE. For intra-pleural delivery, it will be reconstituted in 50ml of sterile 0.9% saline prior to instillation into the pleural cavity.

OK432 is an unlicensed product in the UK. It is licensed in Japan, South Korea and Taiwan for the topical treatment of lymphangiomas and head and neck cancers, and for intra-cavitatory treatment of malignant pleural effusions and ascites.^81-84^ It has been used in routine clinical care as a pleurodesis agent for malignant pleural effusions and refractory pneumothoraces since 1975 in these countries.

Intra-pleural OK-423 is associated with a few specific side effects, including a mild, transient fever and pain following injection. These adverse events are commonly seen with many pleurodesis agents, and are likely to represent pleural inflammation. Other side effects seen with OK432 include malaise and anorexia, but these have always been reported as mild and self-limiting. There have been no reported deaths related to OK432 treatment.

The dose of OK432 used in TILT is 10KE. However, it is permissible to use a reduced dose of 5KE in patients who are a high risk of adverse events, or who would find it difficult to manage an adverse event. For example, elderly patients, patients with performance status of 2-3, patients with multiple medical co-morbidities, especially cardiac or renal, and patients who live alone or have high care needs at home. The decision to use the reduced dose should be made by the treating clinician prior to IMP administration, and can be discussed with the Chief Investigator if desired.

## Arm 2 – BCG

BCG is a live attenuated, low virulence strain of mycobacterium Bovis prepared from a culture of Bacillus Calmette-Guérin (OncoTice, Merck Sharp & Dohme Ltd, The Netherlands). It comprises a freeze-dried preparation of bacilli, with each 12.5mg vial containing 2-8 x 10^8^ colony forming units (CFU). It is supplied as a dry powder, which will be reconstituted in 50ml of sterile 0.9% saline prior to instillation into the pleural cavity. 1ml of the reconstituted solution, containing 0.4-1.6 x 10^7^ CFU, will be delivered intra-pleurally. A reduced dose of 0.5ml (0.2-0.8 x 10^7^ CFU) can be used in patients who are a high risk of adverse events, or who would find it difficult to manage an adverse event. For example, elderly patients , patients with performance status of 2-3, patients with multiple medical co-morbidities, especially cardiac or renal, and patients who live alone or have high care needs at home. The decision to use the reduced dose should be made by the treating clinician, and can be discussed with the Chief Investigator, or responsible delegate ([name]) if desired.

BCG does not have marketing authorisation for intra-pleural use in the UK. However it has been used as an intra-cavitory treatment for bladder cancer since the 1970s. Common adverse events following intra-vesical delivery include local inflammatory effects e.g. cystitis, dysuria, haematuria and systemic inflammatory symptoms including fever, malaise, fatigue and flu-like symptoms. It is anticipated that similar effects will be seen with intra-pleural delivery, with pleuritis, pain and bloody effusions as manifestations of local inflammation. Other common effects from intra-vesical delivery include local infection, nausea and vomiting, and arthralgia & myalgias. Uncommon adverse events include disseminated BCG infection, granulomatous hepatitis and rashes.

BCG has previously been used intra-pleurally in trials of patients following thoracic surgery for lung cancer. Transient fevers, rigors and malaise were common, as with intra-vesical delivery. Additional common adverse events were empyema, infected surgical wounds causing fistulation and late BCG pleural infection (>6 months after delivery).^70 72^ This is likely to reflect the recent major thoracic surgical intervention undergone by participants in these studies. To minimise the risk of infection, either BCG-related or bacterial, recent thoracic surgery or pleural intervention is an exclusion criteria for TILT.

Some studies gave participants prophylactic isoniazid following intra-pleural BCG, however there was no difference in adverse event rates between the trials that did and did not use prophylaxis, and it was concluded that isoniazid had no effect in reducing adverse events.^70^ For this reason, and because isoniazid toxicity is increased in people over the age of 50, prophylactic isoniazid will not be given in TILT.

## Intervention visit

Participants who are randomised to bacterial immunotherapy will be invited to receive a single administration of OK432 or BCG, depending on which arm they are allocated to. The dose of OK432 is 10KE and the dose of BCG is 0.4-1.6x10^7^ CFU.. However, reduced dose options (5KE of OK432 and 0.2-0.8 x 10^7^ CFU of BCG) can be used (based on the discretion of the treating clinician) in older patients, those with higher performance status, people with multiple medical co-morbidities, or those at higher risk of experiencing or not coping with an adverse event. The immunotherapy agent will be delivered intra-pleurally via an indwelling pleural catheter within 14 days of random selection (i.e. days 0-14).

For the intervention visit, participants will attend hospital and undergo medical assessment to ensure they remain eligible and suitable to receive OK432/BCG. This will include complete drainage of the effusion, to ensure IPC patency, followed by a CXR to exclude trapped lung. If they remain eligible, up to 3mg/kg of 1% lignocaine (to a maximum of 250mg) will be instilled intra-pleurally followed by the appropriate agent, in adherence with the Trial Specific Protocol 4 (TSP 04). The IPC will then be disconnected and OK432/BCG left within the pleural cavity for 1 hour. After 1 hour, further drainage will be undertaken and the participant will be observed for another hour before returning home.

Following the intervention, patients will be advised to take regular prophylactic paracetamol and ibuprofen for the subsequent 3 days to reduce the risk of fevers, sweats and pain.

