### 8.2.2 IPC drainage

IPC drainage will take place in the community, either by district nurses or a trained family member or next of kin. If there are no community resources available to perform drainage, the participant may be drained at their local trial centre.

The drainage regimen will be dictated by clinical need and will be decided by the treating clinician in conjunction with the patient and community team. It is expected that most patients will require drainage approximately 2-3 times per week. Drainage diaries will be kept by all participants.

Participants in the bacterial immunotherapy arms will undergo complete drainage prior to IMP delivery to ensure the drain is patent, and to exclude underlying trapped lung.

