# TRIAL FOLLOW UP ASSESSMENTS

## Trial visits

As well as an initial screening visit at Week 0, participants will attend 3 trial assessment visits within the subsequent 12 weeks, with participants in the intervention arm returning for two additional visits; one to receive OK432/BCG within 14 days of randomisation (i.e. days 0-14) and a follow-up safety visit on day 3 post-IMP administration. Trial visits will take place at 3 weeks, 6 weeks and 12 weeks post-randomisation.

Participants who receive an IMP will also be contacted by telephone by a member of the trial team, daily for up to 5 days after IMP administration, to check on their well-being. Trial visits must occur as scheduled +/- 3 days, with the exception of the 3 day post intervention visit which must occur on day 3. Trial procedures and assessments for each visit are detailed in section 9.7. The trial flowchart is shown in section 2.4.

Having completed the 12 week trial period, participants will return to clinical follow up as part of the ASSESS-meso. They will participate in ongoing data collection in accordance with the ASSESS-meso protocol which will continue until death, loss to follow up or withdrawal from ASSESS-meso.

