## End of trial (EoT)

Trial recruitment will cease in November 2019, regardless of the number of participants enrolled. EoT date, therefore, will be 12 weeks after enrolment of the 12^th^ trial patient or 12 weeks after the recruitment window closes, whichever happens first. At EoT, participants will return to clinical follow up within ASSESS-meso, which will continue until death, loss to follow up or withdrawal from the study. Data from ASSESS-meso will be used to evaluate overall survival at EoT.

|  |  | **Screening**  **Week 0*** | **Intervention**  **Day 0-14** | **3 days post-intervention**  **(Week 3)** | **Week 6** | **Week 12** |
| --- | --- | --- | --- | --- | --- | --- |
| **Clinical assessment** | Assessment of eligibility | X | **X** |  |  |  |
|  | History of pleural interventions | X |  | X | X | X |
|  | Previous oncological treatment | X |  |  |  |  |
|  | Medication history | X | **X** | X | X | X |
|  | WHO/ECOG performance status | X | **X** | X |  |  |
|  | Vital signs, pulse oximetry | X | **X** |  |  |  |
|  | Physical examination | X |  |  |  |  |
|  | Insertion of IPC (if not already in situ) | X |  |  |  |  |
|  | Pleural fluid drainage diary review | X |  | X | X | X |
|  | Documentation of AEs |  | **X** |  | X | X |
| **Blood tests** | Screening blood tests (HIV screen, hepatitis screen, immunoglobulins, random glucose, thyroid function tests) | X |  |  |  |  |
|  | Pregnancy test  (if female <55 yrs) | X |  |  |  |  |
|  | Coagulation panel | X |  |  |  |  |
|  | Trial blood tests (Full blood count, urea & electrolytes, liver function tests, C reactive protein) | X | **X** | X | X | X |
|  | Serum mesothelin | X |  | X | X | X |
|  | Pleural fluid sampling and storage | X | **X** | X | X | X |
|  | Mantoux test (if logistically possible, BCG arm only) | X |  |  |  | X |
| **Randomisation & intervention** | Random selection | X |  |  |  |  |
|  | Informed consent for TILT |  | **X** |  |  |  |
|  | Administration of OK432/BCG |  | **X** |  |  |  |
| **PROMS** | Breathlessness & chest pain VAS score | X |  | X | X | X |
|  | Daily VAS score completion |  |  |  |  |  |
|  | EQ-5D-5L QoL questionnaire | X |  | X | X | X |
| **Radiological imaging** | Chest x-ray | X | **X** | X | X | X |
|  | Thoracic ultrasound | X | **X** | X | X | X |
|  | CT chest (within preceding 2 weeks) | X |  |  |  | X |
| **Qualitative research** | Participant interviews |  |  |  |  | X |
|  | Focus groups with relatives/carers |  |  |  |  | X |

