## Analysis plan

Basic descriptors will be used to summarise the characteristics of the overall trial population, each arm, and participants who decline any element of the trial. The characteristics of people who decline participation will be compared with the trial population using means, confidence intervals, chi-squared and unpaired T-tests. If possible, multivariable regression modelling will be undertaken to explore which factors were associated with non-acceptance of OK432/BCG.

Feasibility outcomes, including recruitment, randomisation and trial completion rates, will be described for the overall trial and for each arm. Secondary outcomes will be summarised for each arm based on randomisation, i.e. intention to treat. Per protocol and compliance averaged causal effects (CACE) analysis will be undertaken as secondary analyses for clinical efficacy outcomes.

Time to event data will be analysed using the Kaplan-Meier method. Cox proportional hazards modelling will be used to calculate hazard ratios for death and pleurodesis. Univariable modelling will be used, followed by multi-variable methods to control for potential confounders. The time-independent confounders to be considered are age, sex, performance status, tumour histology and whether chemotherapy was received. Time-dependent confounders that will be adjusted for are the time between diagnosis with MPM and baseline assessment, and length of time the IPC was in situ. The main analysis will include all patients. A priori sub-group analyses will stratify patients according to time since diagnosis (≥8 weeks versus <8 weeks) and whether chemotherapy was received.

Pleurodesis rates will be calculated for the whole population, and in the sub-group of patients who’s IPC had been in situ for less than 6 weeks at baseline assessment.

Outcomes with repeat measurements, e.g. PROMS and biomarker responses, will be analysed using regression modelling with adjustment for baseline values. Survival rates will be compared with national survival data, and survival rates from previous clinical trials of new treatments in MPM. Progression-free survival rates will be compared to validated values for acceptable clinical activity of new oncological agents in MPM.^99^

Statistical analysis will be undertaken using Stata (StataCorp LP) version 14, with support from YTU.

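### Eligibility is re-checked after randomisation only in the OK432 and BCG arms, so an ordinary per-protocol comparison would set re-screened treated patients against controls who were never re-screened

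*Protocol*

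**What the plan says.** Random allocation happens at Week 0 (Protocol, Random selection). Trial visits then separates the groups, "with participants in the intervention arm returning for two additional visits; one to receive OK432/BCG within 14 days of randomisation". At that visit, "participants will attend hospital and undergo medical assessment to ensure they remain eligible and suitable to receive OK432/BCG", and the content is specified: "This will include complete drainage of the effusion, to ensure IPC patency, followed by a CXR to exclude trapped lung". Dosing depends on the result: "If they remain eligible, up to 3mg/kg of 1% lignocaine (to a maximum of 250mg) will be instilled intra-pleurally followed by the appropriate agent" (all Intervention visit). Section 8.2.2 IPC drainage ties the drainage to the active arms: "Participants in the bacterial immunotherapy arms will undergo complete drainage prior to IMP delivery".

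In the schedule of visits, the row "Assessment of eligibility" is marked at screening and at the intervention visit, and nowhere later. Under Consent, controls follow visits matched to the TILT assessment schedule, but they have no intervention visit. Their later chest X-rays and ultrasound scans follow no required complete drainage and have no consequence for eligibility.

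The Analysis plan summarises secondary outcomes by randomised arm first. It then adds: "Per protocol and compliance averaged causal effects (CACE) analysis will be undertaken as secondary analyses for clinical efficacy outcomes".

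**The concern.** The re-check is a filter applied after randomisation, on one side only. A selected patient found to have trapped lung, or otherwise no longer suitable, is not dosed and so leaves any per-protocol set in the usual sense. The equivalent control is never identified and stays in. The two groups are then no longer comparable, even if treatment does nothing.

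The filter is likely to be related to outcome. Trapped lung bears on pleurodesis, which is one of the efficacy outcomes, and general suitability bears on early death and progression. Some patients may be randomised without a catheter and have one inserted after baseline (8.2.1 IPC insertion). For them, catheter patency and lung expansion after drainage through the catheter can be learned only after allocation.

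The use of the data is what is at stake. Secondary outcome measures says that these data will help to choose the primary outcome of the full-scale trial, and the Abstract says that results will inform whether one or both agents go forward.

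**Working it through.** The protocol gives no figure that depends on this point, so there is none to reproduce. The target of 12 has no stated power or effect size behind it. Only the split can be checked: 12 × 2/3 = 8 offered an agent, and 12 / 3 = 4 per arm at 1:1:1, which is consistent.

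**Inputs.** The structure comes from the protocol: randomise at Week 0, re-check the active arms only, dose those who pass. The rates are assumptions, because the protocol gives none:
- f, the share of randomised patients who would fail the re-check: 10%, 20%, 30%;
- pE, the pleurodesis rate in those who would pass, and pF, the rate in those who would fail: (50%, 25%), (60%, 30%) and, as the extreme case, (50%, 0%).

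**Contrasts with no treatment effect.**
- Controls, all retained: (1 − f) × pE + f × pF.
- Treated per-protocol set, only those who pass: pE.
- Per-protocol difference: pE − [(1 − f) × pE + f × pF] = f × (pE − pF).
- Intention to treat: both sides equal (1 − f) × pE + f × pF, so the difference is 0.
- CACE with failures kept as randomised non-compliers: 0 / (1 − f) = 0.

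False per-protocol gain in percentage points:

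| f | pE 50%, pF 25% | pE 60%, pF 30% | pE 50%, pF 0% |
|---|---|---|---|
| 10% | 2.5 | 3 | 5 |
| 20% | 5 | 6 | 10 |
| 30% | 7.5 | 9 | 15 |

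For example, f = 20% with (50%, 25%) gives a control rate of 0.8 × 50 + 0.2 × 25 = 45%, against 50% in the treated set: a gain of 5 points.

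**How often it would arise.** The chance that at least one of the 8 selected patients fails is 1 − (1 − f)^8. This is 0.34 at f = 5%, 0.57 at 10%, 0.83 at 20% and 0.94 at 30%. One failure removes 1/4 = 25% of an arm.

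**Survival and PFSR.** The same selection operates, but a second asymmetry lies beside it. Controls may receive chemotherapy or immunotherapy, although delay to the end of the 12 weeks is preferred (Permitted medications). Patients who receive the intervention may not (Non-permitted medications). This can pull the other way, so no net figure can be derived.

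**The case against.** The strongest reply is that the protocol does not define its per-protocol set, and that a definition may properly sit in a statistical analysis plan that is not shown. That disposes of any complaint about a missing definition. It does not dispose of this point, because the protocol itself fixes both the one-sided check and the per-protocol analysis. No later definition can remove from the control arm patients whom nobody identified.

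The second reply is that intention to treat comes first, CACE is already planned, the primary outcome is feasibility, and the contrast is too noisy to matter. With 4 per arm and a rate of 50%, the standard error of a difference is √(2 × 0.25 / 4), about 35 points, which exceeds the whole range of bias above. This stands and sets the priority.

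A reader might infer more than the documents support:
- *That the comparison must favour treatment on survival and PFSR.* The differing rules on chemotherapy and immunotherapy leave the sign open. Patients who decline also leave the dosed group, with unknown prognosis.
- *That infection or a blocked catheter removes a patient.* The exclusion criteria speak of deferring treatment for infection, and 8.2.3 IPC blockage provides for unblocking. Neither leads automatically to no dose.
- *That the screening blood results can act only after allocation.* The schedule places these tests at Week 0 beside the eligibility assessment and says nothing of late results.
- *That judging trapped lung at Week 0 would cure the problem.* Trapped lung is already an exclusion criterion, and a Week 0 X-ray is scheduled for everyone. Where the effusion is undrained, that film may not show whether the lung re-expands. The stratification sentence mentions drainage, but it is incomplete and concerns performance status.

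**Conclusion.** The point holds in limited form. An ordinary per-protocol comparison with controls would be selected on one side after randomisation. For pleurodesis, this mechanism taken alone favours OK432 and BCG whenever patients who would fail the re-check do worse than those who would pass. The size is 2.5 to 15 points under the assumed inputs; the upper end requires f = 30% and no pleurodesis at all among failures. For survival and PFSR the comparison is not trustworthy, but its direction is unknown.

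The summaries by randomised arm do not suffer from this selection. Neither does CACE, provided that undosed selected patients stay in their arm as non-compliers and its usual assumptions are met. The feasibility conclusions are untouched. Low priority.

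**What to change.** In 13.3 Analysis plan, state that intention to treat and the CACE analysis already planned are the only comparisons with controls. In CACE, patients who fail the re-check and patients who decline are kept as randomised non-compliers. Replace the per-protocol comparison with an uncontrolled description of outcomes in dosed patients, and report the number of re-check failures and their reasons by arm.

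The pre-dose check stays exactly as it is, and no procedure is added. The cost is a small edit to one section and one secondary comparison fewer. CACE already addresses the question of what dosing does in those who receive it.

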# TRIAL METHODOLOGY

## Trial setting

The trial will be conducted at 3 hospitals with specialised pleural disease services ; North Bristol NHS Trust (NBT), Oxford Centre for Respiratory Medicine (OCRM) and Musgrove Park Hospital, Taunton.

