## Sample size & recruitment targets

The target sample size is 12 participants, of whom 8 will be randomly selected to be offered OK432 or BCG and 4 will continue in ASSESS-meso as controls. This sample size is based on previous feasibility studies in mesothelioma.

It is anticipated that the majority of participants who are offered bacterial immunotherapy will consent to receive it, as the burden of treatment is low (a single dose on one occasion), the treatment intervention is well established in other clinical scenarios and trial follow up assessments are the same as they would be within ASSESS-meso. Non-acceptance of bacterial immunotherapy will be collected as part of the feasibility outcomes for the trial, and qualitative interviews will explore these participants’ reasons for non-acceptance of bacterial immunotherapy.

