## Permitted medications

Participants are expected to continue the use of prescribed medications during the course of the study, as identified at baseline assessment, and consistent with study inclusion and exclusion criteria. In addition, all treatments that are considered necessary for a participant’s welfare may be administered at the discretion of the treating clinician or trial investigator in keeping with standard medical practice.

Participants in both arms will receive best supportive care alongside the investigational products, with the exception of oral steroids, which should be avoided, if possible, in the 14 days before and after OK432/BCG delivery. Analgesia, anti-emetics and antipyretics can be given as required, in accordance with local prescribing guidelines.

The following medications will be delivered to all participants who receive OK-423 or BCG, as stated in the trial manual:

- Up to 200mg 1% Lignocaine administered intra-pleurally contemporaneously with OK432/BCG delivery.
- Paracetamol, oral or intra-venous to a maximum dose of 4g per 24 hours, delivered immediately prior to OK432/BCG delivery and as required subsequently
- Opioid analgesia, including oral codeine phosphate 30-60mg to a maximum of 240mg in 24 hours, or oral morphine sulphate at a dose that is appropriate to the participant’s current and previous use of morphine, delivered immediately prior to OK432/BCG delivery and as required subsequently
- Medications to treat any treatment-emergent AEs

Medications to treat treatment-emergent AEs should not interfere with the study and can be used at the investigator’s discretion. Antipyretics and anti-inflammatories may be used to treat fever or to prevent recurrence of fever.

Subjects with clinical symptoms or signs of infection should have a clinically relevant evaluation, including appropriate bacterial cultures. If pleural infection is suspected, a sample of pleural fluid should be taken and sent for biochemical and microbiogical assessment. If antibiotics are required, in the opinion of the treating clinician, local guidance should be followed, to include gram positive and anaerobic cover. The preferred regimen would include either co-amoxiclav or Tazocin. The decision regarding intra-venous or oral treatment should be made by the treating clinician.

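### Sections 7.3 and 8.3 set different intra-pleural lignocaine ceilings for the same administration, and they agree only at a body weight of 66.7 kg

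*Protocol*

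**What the plan says.** Section 7.3 (Intervention visit) describes how the agent is given. After drainage and a chest X-ray, and before the agent itself, "up to 3mg/kg of 1% lignocaine (to a maximum of 250mg) will be instilled intra-pleurally". The section refers the procedure to TSP 04. It covers one event per person, since each participant "will be invited to receive a single administration of OK432 or BCG, depending on which arm they are allocated to".

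Section 8.3 (Permitted medications) lists what accompanies the agent. It opens with "The following medications will be delivered to all participants who receive OK-423 or BCG, as stated in the trial manual", and its first item is "Up to 200mg 1% Lignocaine administered intra-pleurally contemporaneously with OK432/BCG delivery". That item has no limit per kilogram.

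Section 6.6 gives a target of 12 participants, "of whom 8 will be randomly selected to be offered OK432 or BCG". Section 6.1 adds: "The trial will be conducted at 3 hospitals with specialised pleural disease services".

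**The concern.** Both sections set a maximum for the same drug at the same strength, by the same route, at the same visit and in the same people. The maxima differ in size and in form: one depends on weight and carries a cap, and the other is a flat figure. The protocol contains no rule of precedence.

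What is at stake is a dosing limit that site staff have to apply at the visit where the trial agent is given. Someone working from Section 8.3 alone could exceed 3 mg/kg in a lighter participant. Someone working from Section 7.3 alone could exceed 200 mg in a heavier one. A monitor checking compliance could not say which of these is a deviation. Each section also refers to a differently named supporting document, TSP 04 in one and the trial manual in the other. Neither is shown, so they may or may not carry a single limit.

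**Working it through.** **Inputs**

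- Section 7.3: ceiling = min(3 mg/kg × weight, 250 mg).
- Section 8.3: ceiling = 200 mg at any weight.
- Both specify a 1% solution, which is 10 mg/ml, so 250 mg is 25 ml and 200 mg is 20 ml.

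The plan has no derived figure of its own to reproduce here. The check compares two stated limits.

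**Where the ceilings meet**

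- They are equal where 3 × weight = 200, so weight = 200/3 = 66.7 kg.
- The 250 mg cap in Section 7.3 starts where 3 × weight = 250, so weight = 250/3 = 83.3 kg.
- Below 66.7 kg Section 8.3 is the more permissive. Above 66.7 kg Section 7.3 is.

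**Ceilings by weight (illustrative; the documents give no body weights)**

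| Weight | Section 7.3 | Section 8.3 | 7.3 minus 8.3 | 200 mg as mg/kg |
| --- | --- | --- | --- | --- |
| 50 kg | 150 mg | 200 mg | −50 mg | 4.0 |
| 60 kg | 180 mg | 200 mg | −20 mg | 3.33 |
| 66.7 kg | 200 mg | 200 mg | 0 | 3.0 |
| 70 kg | 210 mg | 200 mg | +10 mg | 2.86 |
| 80 kg | 240 mg | 200 mg | +40 mg | 2.5 |
| 83.3 kg | 250 mg | 200 mg | +50 mg | 2.4 |
| 100 kg | 250 mg | 200 mg | +50 mg | 2.0 |

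The most by which Section 7.3 can exceed Section 8.3 is 250 − 200 = 50 mg, or 25 − 20 = 5 ml.

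**Can both limits be meant?** If both applied, the ceiling would be min(3 × weight, 250, 200) = min(3 × weight, 200). The 250 mg maximum would then never bind at any weight. Its presence shows that the two figures were not written to be used together.

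**A dose that satisfies both** is at most min(3 × weight, 200): 150 mg (15 ml) at 50 kg, 180 mg (18 ml) at 60 kg, and 200 mg (20 ml) from 66.7 kg upward.

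**The case against.** The best reply is that the sections do not carry equal weight. Section 7.3 is the working instruction for giving the agent. Section 8.3 sits under non-trial treatments and is a loose list: it is said to go to every recipient, yet it includes drugs to treat adverse events, which not everyone will need. Staff who follow Section 7.3 never exceed 3 mg/kg. Both figures are upper limits, so a compliant dose exists at every weight. TSP 04 may be part of the trial manual and may already fix one dose. The documents give no toxicity threshold and no reason for either number, and the difference is small and arises once per person.

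Much of this stands. It limits the weight of the point: no harm can be shown, and the supporting documents might settle practice. It does not remove the contradiction. The protocol does not rank Section 8.3 below Section 7.3, and Section 8.3 says that its list applies to every recipient. That a dose satisfying both can be worked out does not help a reader who sees only one of them. A correct figure in an unseen document would leave the protocol wrong as written.

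**Conclusion.** The inconsistency is real and should be fixed. The two ceilings agree only at 66.7 kg. Section 8.3 is the looser below that weight (by 50 mg at 50 kg), and Section 7.3 is the looser above it (by up to 50 mg, or 5 ml, from 83.3 kg). At least one of the limits is not the intended one.

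The effect is confined to the dosing of an accompanying anaesthetic. Under the Section 6.6 target it concerns at most 8 people, and fewer if some decline treatment. How many fall on each side of 66.7 kg cannot be known from the documents. Nothing here touches the dose of OK432 or BCG, the feasibility criteria, the sample size or the analysis.

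The conclusion rests on reading both sections as governing the same instillation. The shared drug, strength, route, timing and recipients, and the single administration, support that reading.

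**What to change.** State one ceiling, in identical words, in Sections 7.3 and 8.3, with both a limit per kilogram and an absolute cap. Alternatively, state it in Section 7.3 and have Section 8.3 refer to it. The clinical and pharmacy leads should confirm the intended maximum, because the documents give no basis for choosing between 200 mg and 250 mg. TSP 04 and the trial manual should then be checked against the confirmed figure.

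Until that is done, use the lower of 3 mg/kg and 200 mg. This complies with both sections at every weight and needs no new procedure.

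The cost is one line in each of two sections and a check of the supporting documents. The interim rule lowers the ceiling that Section 7.3 now allows above 66.7 kg, by up to 50 mg (5 ml). For heavier participants that could mean less local anaesthetic before a procedure after which chest pain is an expected reaction (Section 12.5), so the intended figure should be confirmed promptly.
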